## Abstract

**Background:**

There is growing evidence of the treatment efficacy of cognitive behavioral therapy (CBT) for irritable bowel syndrome (IBS). CBT is recommended by several practice guidelines for patients with IBS if lifestyle advice or pharmacotherapy has been ineffective. Manual-based CBT using interoceptive exposure (IE), which focuses on the anxiety response to abdominal symptoms, has been reported to be more effective than other types of CBT. One flaw of CBT use in general practice is that it is time and effort consuming for therapists. Therefore, we developed a set of complementary video materials that include psycho-education and homework instructions for CBT patients, reducing time spent in face-to-face sessions while maintaining treatment effects. The purpose of this study is to examine the effects of CBT-IE with complementary video materials (CBT-IE-w/vid) in a multicenter randomized controlled trial (RCT).

**Methods:**

This study will be a multicenter, parallel-design RCT. Participants diagnosed with IBS according to the Rome IV diagnostic criteria will be randomized to either the treatment as usual (TAU) group or the CBT-IE-w/vid + TAU group. CBT-IE-w/vid consists of 10 sessions (approximately 30 min face-to-face therapy + viewing a video prior to each session). Patients in the CBT-IE-w/vid group will be instructed to pre- view 3- to 13-min videos at home prior to each face-to-face therapy visit at a hospital. The primary outcome is the severity of IBS symptoms. All participants will be assessed at baseline, mid-treatment, post-treatment, and follow-up (3 months after post assessment). The sample will include 60 participants in each group.

**Discussion:**

To our knowledge, this study will be the first RCT of manual-based CBT for IBS in Japan. By using psycho-educational video materials, the time and cost of therapy will be reduced. Manual based CBTs for IBS have not been widely adopted in Japan to date. If our CBT-IE-w/vid program is confirmed to be more effective than TAU, it will facilitate dissemination of cost-effective manual-based CBT in clinical settings.

**Trial registration:**

The trial was registered to the University Hospital Medical Information Network Clinical Trial Registry: UMIN, No. UMIN000030620 (Date of registration: December 28, 2017).

## Introduction

Irritable bowel syndrome (IBS) is a common chronic functional gastrointestinal disorder that affects about 14% [1] of the Japanese population. Symptoms of IBS such as abdominal pain and altered bowel habits (i.e., constipation and/or diarrhea) interfere with the patient’s quality of life (QOL) [2] and social functioning [3, 4]. IBS is associated with a significant increase in time off work [5] and increased health care use. Severity of abdominal pain/discomfort is a significant predictor of health care use for patients with IBS compared with non-IBS subjects [6]. Annual medical expenses paid for patients with IBS were reported to be 50% higher than those for population-controlled non-IBS patients [7].

Evidence for IBS treatment efficacy using cognitive behavioral therapy (CBT) has been growing [8–10]. Systematic reviews and meta-analysis have repeatedly confirmed CBT efficacy for IBS [11, 12]. Treatment guidelines issued by the National Institute of Clinical Excellence (NICE) in the United Kingdom recommend introducing CBT if lifestyle advise or pharmacotherapies have been ineffective and symptom duration has exceeded 12 months [13]. Specific psychotherapies including CBT are also recommended in the clinical guideline issued by the Japanese Society of Gastroenterology as the third step of IBS treatment that has been refractory to the first step (lifestyle advise and gut-targeted pharmacotherapies) and second step (psychopharmacological agents and brief psychotherapies) treatments [14]. However, CBT for IBS is available only in specific centers in Japan and evidence of its efficacy has not been established here. Therefore, RCT evidence of efficacy for CBT for patients with IBS is needed.

Among the several CBT programs reported for IBS, we adopted the interoceptive exposure-based CBT program (CBT-IE) for IBS developed by Craske et al. [15]. CBT-IE for IBS includes exposure to abdominal sensations in addition to psychoeducation, self-monitoring, cognitive restructuring, attention training, and in vivo exposure, which are often used in traditional CBT. Patients are exposed to self-induced abdominal sensations (e.g., by tightening abdominal muscles, or consuming avoided foods, etc.) to reduce anxiety in response to abdominal disturbance common in IBS.

Interoceptive exposure (IE) was originally developed for panic disorder [16], and its clinical applications have been expanded. IE is considered to weaken the fear response by enabling new learning that competes with the initial fearful associations [17]. It has been suggested that gastrointestinal symptom-specific anxiety (GSA) is important in perpetuating IBS. GSA has been shown to predict symptom severity and QOL in IBS. The effect on IBS symptoms and QOL of interventions using exposure that targets GSA has been supported by previous studies [18, 19], and its superiority over active treatment controls has been shown in some RCTs [15, 20].

Our single-arm feasibility study of CBT-IE for Japanese IBS patients [21] indicated significant reduction of IBS symptoms and remarkable improvement in IBS-specific QOL at post-intervention, 3-month, and 6-month follow-ups compared with the pre-intervention state. Although CBT-IE appears to be a promising treatment for refractory IBS, there are some difficulties in disseminating this intervention to clinical settings in Japan, including the limited number of CBT therapists and the highly time-consuming process of CBT [11].

To reduce the implementation costs, we developed a set of complementary video materials that cover psychoeducation and homework instructions regarding treatment so that patients can prepare at home for the subsequent in hospital, face-to-face therapy. The treatment procedures and contents are the same as with the original CBT-IE. Our additional feasibility study indicated that use of the video material with CBT-IE reduced the time spent in face-to-face therapy by about 40% on average, while treatment effectiveness remained constant. We calculated effect sizes (Hedges’ g) for changes in the Japanese version of the IBS Severity Index (IBS-SI-J) before and after the CBT-IE intervention. The effect size of our first feasibility study of face-to-face therapy alone [21] was g = − 1.02 (*N* = 20, session time: 66 ± 7 min), and the effect size of our second feasibility study using video material [22] was g = − 0.99 (*N* = 8, session time: 38 ± 7 min).

### Research objectives and hypotheses

An RCT will be done to examine the efficacy of CBT-IE with complementary video material (CBT-IE-w/vid) for Japanese patients with moderate to severe refractory IBS patients. The hypothesis is that participants allocated to the CBT-IE-w/vid + TAU group will have significantly reduced symptoms compared to the participants in the TAU alone group.

## Methods

This multicenter RCT will be conducted by a multidisciplinary team of medical doctors who specialize in psychosomatic medicine and functional gastrointestinal disorders, clinical psychotherapists, researchers, and statisticians.

### Design

A multicenter randomized controlled trial with two equal-sized parallel groups at five centers.

Potential participants will be screened for eligibility and will give written informed consent to participate. All participants will be assessed at baseline and then individually randomized into the CBT-IE-w/vid + TAU or TAU alone groups. Participant flow is depicted in Fig. 1.

**Fig. 1 Fig1:**
[figure not shown]
Flow of participants through the study

All assessment measures, except for screening, are self-report questionnaires. Participants will complete baseline (pre-treatment), mid-treatment, post-treatment, and 3-month follow-up assessments. This protocol has been reviewed and approved by the Institutional Review Board of the National Center of Neurology and Psychiatry (accepted on November 29, 2017; A2017–067) and by the Ethics Committees of the four other collaborating facilities. The trial has been registered in the University Hospital Medical Information Network (UMIN) Clinical Trials Registry (URL: http://www.umin.ac.jp), No. UMIN000030620.

### Setting

Participants assigned to the CBT-IE-w/vid + TAU group will receive the standard IBS treatment from a medical doctor and face-to-face CBT-IE sessions with a therapist (a clinical psychotherapist or medical doctor who specializes in psychosomatic medicine) at a hospital. In addition, participants in the CBT-IE group will be instructed to watch the complementary video material and complete homework at home. Participants in the TAU alone group will receive the standard IBS treatment from a medical doctor at the hospital.

The intervention will be conducted at outpatient units of the five collaborating hospitals: National Center Hospital, National Center of Neurology and Psychiatry, Tohoku University Hospital, the University of Tokyo Hospital, Center Hospital of the National Center for Global Health and Medicine, and Kohnodai Hospital, National Center for Global Health and Medicine in Japan.

### Target population

Participants will be recruited from the five hospitals listed above and will include 120 outpatients aged 16 years or older with an IBS diagnosis according to the Rome IV diagnostic criteria and moderate to severe IBS symptoms based on IBS-SI-J scores.

### Recruitment

Recruitment will be conducted at each center by advertising and referrals from health care professionals. When a health care professional deems CBT-IE-w/vid feasible for the patient, the patient will be informed of this trial and referred to the trial team of each center.

### Screening

The initial screening will be conducted by medical doctors of the trial team of each center, all of whom specialize in psychosomatic medicine. After the patients give informed consent, eligibility will be evaluated according to the inclusion and exclusion criteria. Eligible participants will be provisionally registered, subjected to the baseline outcome assessment, and then definitively registered.

### Eligibility criteria

#### Inclusion criteria

To be eligible to participate in this study, a participant must meet all of the following criteria:Aged 16 years or older with IBS that is refractory to standard pharmacotherapyDiagnosed with IBS based on the Rome IV diagnostic criteria [23]The severity of IBS is moderate or severe (IBS-SI-J score: 175 or over) [24, 25]Able to understand the purpose and contents of this trial and give voluntary written informed consent

#### Exclusion criteria

A potential participant who meets any of the following criteria will be excluded from participation:Organic disease suggested by the presence of warning symptomsA history of concomitant inflammatory bowel disease, malignant tumor, or other bowel disease which could cause the current bowel symptomsA comorbidity of major psychiatric disease, such as psychotic disorders, bipolar disorder, substance abuse-related disorders, eating disorders, obsessive and compulsive disorders, or PTSD. However, persons with anxiety disorders, somatic symptoms, related disorders, or depression without suicidal ideation will not be excluded. The screening for this part will be conducted using the Mini International Neuropsychiatric Interview (M.I.N.I.) [26], a widely used structured diagnostic interview that screens for various mental diseases.Antisocial personality disordersSignificant suicidal ideation at screeningPast or present psychiatric or physical disease that is likely to interfere with continuation and evaluation of the studyAny other type of marked chronic painTaking narcotic analgesicsDifficulty in attending 10 sessions as an outpatient during the 16-week CBT implementation periodPreviously received structured individual CBTUnable to understand verbal and written communication in the Japanese languagePregnant or lactating womenAny other person whom the principal investigator has determined to be unsuitable as a participant of the study

Warning symptoms list:Symptoms that first appeared after 50 years of ageAny rectal bleeding that has not undergone sufficient medical investigation (excluding that caused by known hemorrhoids)Diarrhea-predominant IBS in which no colonoscopy investigation has been conductedUnexplained weight loss without a change in eating habitsNocturnal symptoms sufficient to cause insomniaThe presence of warning findings (anemia, positive inflammatory reactions, or positive fecal occult blood)Persons with a family history of colon cancer in a first- or second-degree relative (grandparents, parents, siblings, or children)

#### Participant withdrawal of consent

Participants can withdraw at any time without penalty. Withdrawal information will be collected.

### Randomization

Randomization will be conducted using the Electronic Data Capture System (HOPE eACReSS, Fujitsu ltd.), which can be accessed from each institute via the Internet. The Electronic Data Capture System will be set up and managed independent of the study by the Data Management division at the National Center of Neurology and Psychiatry (NCNP). A random sequence will be generated using stratified randomization by hospital. Eligible participants will be registered at each hospital on a PC terminal connected to the Electronic Data Capture System via the Internet. Allocation to the treatment or control group will be implemented centrally and automatically upon registration and then displayed on the terminal.

### Planned interventions

#### CBT - interoceptive exposure with complementary video materials (CBT-IE-w/vid)

Participants receive CBT using interoceptive exposure for IBS with complementary psychoeducational video materials (CBT-IE-w/vid**)**. The original IE program [15] consists of 10 weekly sessions of approximately 60 min. Our CBT-IE-w/vid intervention consists of 10 weekly sessions, but the time length of each session has been changed. Each session consists of 2 parts: viewing 3- to 13-min videos at home in advance followed by about 30-min of face-to-face therapy session with a therapist at hospital. All CBT-IE-w/vid therapists will be medical doctors who specialize in psychosomatic medicine or psychologists qualified in least one of the following: licensed by the Japanese government, clinical psychologists qualified by the Foundation of the Japanese Certification Board for Clinical Psychologists, or medical psychologists qualified by the Japanese Society of Psychosomatic Medicine.

CBT-IE-w/vid intervention includes (a) education that IBS symptoms reflect conditioned reactions to reminders of gastrointestinal distress (e.g., food intake or a ride on a train); (b) self-monitoring of IBS symptoms; (c) attentional control skills to learn to shift attention away from rather than perseverate upon unpleasant visceral sensations [27]; (d) cognitive therapy to identify threat-laden appraisals of disturbance caused by IBS symptoms; (e) interoceptive exposure involving repeated exposure to visceral sensations (e.g., tightening stomach to produce gut sensations, delaying entrance to the bathroom, eating feared/avoided foods) to reduce fear of the sensations; and (f) in vivo exposure to feared/avoided situations in which IBS sensations were expected (e.g., riding a long-distance train, eating at restaurants, going places where bathrooms are not accessible) while weaning “safety signals” or “safety behaviors” (e.g., keeping medicines handy at all times or carrying additional underclothing). Reliance on safety signals or safety behavior during exposure practices interferes with relearning. Homework, using a paper-based textbook, is required for each session. Table 1 shows the contents of each session, the handout (including homework), and the duration of each video. There is no objective control over the usage of the complimentary video materials. The videos continue to be available after the end therapy, as are texts and materials. Patient usage of video material and homework will be tracked using a compliance check sheet during intervention and at follow up.

**Table 1 Tab1:** Contents of each session

Session number	Contents of intervention	Handouts	Play time of Video
1	Education about IBS and psychological stress on digestive functioning, awareness-raising	• Personal IBS profile (in session use)	(12′ 16″)
		• Monitoring IBS distress	
2	Education about the role of conditioning in IBS, attentional training	• Monitoring IBS distress	(6′ 44″)
		• Guide for Attentional training	
		• Common IBS symptom appraisal list	
3	Attentional training, cognitive restructuring for IBS sensations and risk estimates	• Monitoring IBS distress	(9′ 31″)
		• Common IBS symptom appraisal list	
4	Cognitive restructuring for symptoms of IBS, valence estimates, hierarchy construction for IBS sensation reminders	• Monitoring IBS distress	(9′ 05″)
		• Deliberate exposure hierarchy	
5	Cognitive restructuring, interoceptive exposure assessment, in vivo exposure	• Monitoring IBS distress	(11′ 36″)
		• Interoceptive exposure exercises	
		• Interoceptive exposure FAQ	
		• Guide for IBS and in-vivo exposure	
		• In-vivo exposure instructions	
		• Deliberate exposure record	
6–9	Conduct of Interoceptive exposure, in vivo exposure	• Monitoring IBS distress	(5′ 40″)
		• Interoceptive exposure instructions	(3′ 32″)
		• Interoceptive exposure record	(3′ 43″) (3′ 35″)
10	Interoceptive exposure, in vivo exposure, summary of the all sessions, relapse prevention	• Monitoring IBS distress	(7′ 44″)
		• Relapse prevention Map	
		• Dealing with setbacks	
		• List of positive Accomplishments	

#### Treatment as usual (TAU)

Patients in both treatment arms will receive TAU by medical doctors. TAU is defined as standard treatment for IBS as recommended by the clinical practice guidelines of the Japanese Society of Gastroenterology [14]. According to the guidelines, a three-step strategy is adopted. The first step consists of lifestyle modification and gut-targeted pharmacotherapy for approximately 4 weeks. Non-responders to the first step intervention proceed to the second step, which includes psychopharmacological agents and brief psychotherapy in addition to the first step interventions for approximately 4 weeks. In the third step, for patients who have not obtained sufficient improvement by the second step, specific psychotherapies including CBT are recommended.

In this study, TAU will consist of only the first and second step interventions. Time spent in each TAU session is 15–30 min. The frequency of TAU sessions is usually once every 4 weeks, but it may vary depending on the patient’s schedule. There is no limit for duration of TAU in either arm. This procedure will be beneficial and ethically desirable for patients.

The medical doctor in charge will implement TAU using the common guidance reviewed by IBS experts (SF, KY, and [name]).

#### Quality assurance

To ensure treatment fidelity, CBT-IE-w/vid therapists will have completed designated CBT-IE-w/vid training and will receive continuous support from supervisors (TA, YF) and peer-supervisors (MF, [name]) throughout the study. All CBT-IE-w/vid sessions will be subject to evaluations of treatment adherence and competence using treatment manuals that provide detailed session-by-session guidance to standardize intervention among all therapists, who will complete checklists for session protocols after each session. Therapists will rate patient adherence to homework using a six-point scale [10].

### Discontinuation

Any participant who meets any of the following discontinuation criteria will have their intervention stopped. When possible, subsequent assessment will be conducted.Participant requests discontinuation or participant withdraws consentDifficulty continuing the intervention because of a serious adverse eventParticipant proves after assignment not to fulfill the eligibility criteriaParticipant with suicide riskAny other reason that the primary investigator, the medical doctor, CBT-IE-w/vid therapist, supervisor, or the Data and Safety Monitoring Board agree warrants discontinuationThe entire clinical trial is stopped

## Measures

### Primary outcome measure

***Japanese version of the IBS severity index (IBS-SI-J)***: IBS-SI or IBS severity scoring system (IBS-SSS) was developed in the UK and is widely used to assess the severity of lower gastrointestinal symptoms and the degree to which the quality of life is impaired by IBS. IBS-SI-J is a valid, reliable, and appropriate instrument for detecting and assessing the severity of IBS status in Japanese patients [24, 25]. This self-report instrument has five items that score abdominal pain, abdominal distention, bowel movements, and quality of life. The total score ranges from 0 to 500. IBS severity is graded as mild (75–174), moderate (175–299), or severe (300–500).


Table 2 shows the schedule of assessments of outcomes.

**Table 2 Tab2:**
[figure not shown]
Schedule of assessments

### Sample size

We estimated a sample size of 60 per group (total 120) from standardized treatment effects that were estimated as 0.91 to 1.02 based on the single-arm feasibility study that preceded this study [21]. However, we used a conservative estimate of 0.6 for the standardized treatment effects for between-group differences because the previous randomized control trial [15] with a similar target population and outcomes estimated standardized treatment effects at 0.33 to 0.70. Thus, the minimum required sample size with minimum power set at 0.8 was estimated as 45 subjects per group. We increased this to 60 subjects per group to maintain adequate statistical power in case of potential dropouts.

### Statistical analysis

Statistical analyses will be conducted by an independent statistician (KM) who is not a TAU medical doctor or CBT-IE-w/vid therapist.Analysis set for efficacy analysis: modified intention to treat (ITT) set that includes all subjects who have at least one outcome after intervention.If possible, data from participants who drop out will be collected after dropout.Analysis for background factors: summary statistics (frequency, mean, SD) will be calculated depending on the characteristics of each variable.Primary analysis: mixed model for repeated measures (MMRM) analysis will be applied to the change from baseline for IBSSI-J at visit five (for participants in the TAU alone group the time point is defined as 6 to 10 weeks after randomization) and visit ten (for participants in the TAU alone group the time point is defined as 10 to 16 weeks after randomization), where treatment, visit, treatment-by-visit interaction, and baseline IBSSI-J are modeled as fixed effects. T-tests will then be conducted on the difference of adjusted means between the groups at visit 10.Secondary analyses: MMRM analysis will be applied to other continuous outcomes.

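### If therapists within a hospital differ in results, the planned precision and the 80% power at 45 per group are overstated: the sample size assumes independent participants and the listed MMRM has neither therapist nor hospital

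*Protocol article*

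**What the plan says.** - **Delivery.** Under Setting, the CBT arm receives "face-to-face CBT-IE sessions with a therapist (a clinical psychotherapist or medical doctor who specializes in psychosomatic medicine) at a hospital". The intervention section gives ten sessions, each with "about 30-min of face-to-face therapy session with a therapist at hospital". Therapists may be physicians or psychologists with any one of several qualifications. Both arms receive usual treatment from medical doctors, so the therapist layer exists in the CBT arm only.
- **Design.** There are "two equal-sized parallel groups at five centers", and randomization is stratified by hospital.
- **Sample size.** The plan states "we used a conservative estimate of 0.6 for the standardized treatment effects for between-group differences", and the "minimum required sample size with minimum power set at 0.8 was estimated as 45 subjects per group". The step to 60 has one stated purpose: "We increased this to 60 subjects per group to maintain adequate statistical power in case of potential dropouts". No design effect, ICC or number of therapists appears.
- **Primary analysis.** The Statistical analysis section says "mixed model for repeated measures (MMRM) analysis will be applied to the change from baseline for IBSSI-J". The fixed effects listed are treatment, visit, treatment-by-visit and baseline score, and the test is a t-test on adjusted means at visit 10. Neither therapist nor hospital is listed.
- **Standardization.** Quality assurance describes training, supervision, session-by-session manuals and checklists.

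**The concern.** This is a partially nested design. Patients who share a CBT therapist may have correlated outcomes, and TAU-alone patients have no therapist to share. Doctors giving usual treatment serve both arms, so they do not create the same one-sided clustering. An analysis that treats all participants as independent then uses too small a variance for the CBT-arm mean. At stake are the width of the confidence interval, the true level of the 5% test, and the claim that 45 evaluable per group is enough. The article wants its result to support dissemination, which means inference beyond the particular therapists who took part.

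Hospital is a second, separate omission. It is the stratification factor but not in the listed model, and leaving it out affects the standard error in the other direction.

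**Working it through.** **Inputs from the article:** standardized effect 0.6, power 0.8, 45 per group evaluable, 60 recruited, 1:1 allocation.

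**Assumptions, not in the article:** two-sided alpha 0.05; k = 5, 10 or 15 therapists with equal caseloads; within-hospital therapist ICC 0.02 to 0.10; equal total variance in both arms.

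**1. Reproduce the plan's figure.** An independent two-sample t-test with effect 0.6, two-sided 5% and 80% power needs 44.6, so 45 per group (actual power 80.4%). One-sided 5% gives about 35 and does not match. The 45 therefore contains no allowance for clustering.

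**2. Add clustering in the CBT arm only.** With n = 45 per group and SE in standard-deviation units:

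- Caseload m = n/k; design effect DE = 1 + (m − 1) × ICC
- Naive SE = √(2/n) = 0.2108; true SE = √((DE + 1)/n); ratio r = √((DE + 1)/2)
- Type I error of the naive test = 2·P(T > 1.987/r), T on 88 df
- Power of a test using the true SE: noncentral t on 88 df, noncentrality 0.6/true SE

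| k | ICC | DE | True SE | r | Type I error | Power |
|---|---|---|---|---|---|---|
| 15 | 0.02 | 1 + 2 × 0.02 = 1.04 | 0.2129 | 1.010 | 5.2% | 79.6% |
| 10 | 0.05 | 1 + 3.5 × 0.05 = 1.175 | 0.2198 | 1.043 | 6.0% | 77.0% |
| 5 | 0.05 | 1 + 8 × 0.05 = 1.40 | 0.2309 | 1.095 | 7.3% | 72.9% |
| 5 | 0.10 | 1 + 8 × 0.10 = 1.80 | 0.2494 | 1.183 | 9.7% | 66.2% |

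**3. If nobody is lost (60 per group).**

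- k = 5, ICC 0.05: DE = 1 + 11 × 0.05 = 1.55, SE = √(2.55/60) = 0.2062, power 82% (118 df).
- k = 10, ICC 0.05: DE = 1.25, power 87%.
- k = 5, ICC 0.10: DE = 2.10, power about 75%.

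**4. Cost of the nested test.** Steps 2 and 3 charge nothing for estimating the therapist variance. The Satterthwaite approximation is df = v² / [(DE/n)²/(k − 1) + (1/n)²/(n − 1)], with v = (DE + 1)/n. At n = 45 and k = 5:

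- ICC 0: df = 14.7, power 76%.
- ICC 0.05: df = 11.2, power 66%.
- ICC 0.10: df = 9.4, power 58%.

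With k = 10 and ICC 0.05, power is 75%. With 60 per group, k = 5 and ICC 0.05, it is also 75%.

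**The case against.** **Everything about size is assumed.** This stands. The article gives no ICC, therapist count or caseload for this trial. Its remark about few CBT therapists concerns Japan in general. With 15 therapists and an ICC of 0.02 the effect is negligible. Manuals, supervision and fixed video content favor the low end of the ICC range, though nothing shows the ICC to be zero.

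**The sign is not certain.** A reader might infer that the planned test is certainly too liberal. The documents do not support that. Hospital differences common to both arms are balanced by the stratified randomization, and leaving hospital out tends to make the SE too large. Only therapist variation within hospitals, and treatment effects that vary by hospital, make it too small. The net effect under the listed model is unknown. Relying on two omissions to cancel is still no plan, and once hospital is added the therapist part remains.

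**The model is only partly described.** A reader might also infer that therapist effects will be ignored or that therapist identity is not captured. The article lists fixed effects and says nothing about random effects; an analysis plan not shown may cover them. Therapists already complete a checklist after each session. This objection does not reach the sample size, whose stated figure reproduces only under independence.

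**Sixty are recruited.** True, and that margin would absorb moderate clustering if dropout is low. The article assigns it to dropout, however, so it cannot be counted in full for both. Baseline adjustment and the use of visit-five data may recover some precision, by an amount the article does not allow one to calculate.

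**Conclusion.** The point holds conditionally. The article establishes one-sided nesting by therapist, a sample size that assumes independence, and a listed model without therapist or hospital. If the within-hospital therapist ICC is positive, the therapist component makes the SE of the treatment difference too small, and 45 evaluable per group falls short of 80% power.

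Over the assumed range (5 to 15 therapists, ICC 0.02 to 0.10), the consequence runs from trivial to material; the middle case is modest. The worst figures need about one therapist per hospital together with an ICC of 0.10. The article does not show that the trial is underpowered or that its test is invalid. It shows that the power statement lacks a condition it needs, and that the listed analysis gives no protection if the condition fails.

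**What to change.** 1. Add hospital as a fixed effect to the primary MMRM. This follows the stratified randomization and costs four degrees of freedom.
2. Make sure a therapist ID is held in the trial database for each CBT participant. This is one field, and hard to recover later if it is not captured prospectively.
3. Prespecify a partially nested model, with a random therapist effect in the CBT arm only and small-sample degrees of freedom. Make it a sensitivity analysis, or the primary analysis if there are enough therapists, and fix that choice before outcome data are seen.
4. State the number of therapists and give the power conditional on it over an assumed ICC range, for 45 and for 60 evaluable per group.

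The cost is a wider interval and fewer degrees of freedom in the nested analysis. With about five therapists that is substantial: roughly 76% power at 45 per group even when the ICC is zero. This is the reason not to make the nested model primary regardless of therapist number. Restating power does not restore it. If the conditional figure is judged too low, the remedies are more therapists or more evaluable participants.

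### Randomization is stratified by hospital, but the primary MMRM as listed has no hospital term, so the reported precision does not use the stratification

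*Protocol article*

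**What the plan says.** Under Design, the protocol article describes "A multicenter randomized controlled trial with two equal-sized parallel groups at five centers". Under Randomization it says: "A random sequence will be generated using stratified randomization by hospital". Hospital is the only stratification factor named. The article does not say whether allocation is blocked or otherwise restricted within hospital.

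Under Statistical analysis, the primary model is an MMRM for change from baseline in IBS-SI-J at visits five and ten, in which "treatment, visit, treatment-by-visit interaction, and baseline IBSSI-J are modeled as fixed effects". The decisive comparison follows: "T-tests will then be conducted on the difference of adjusted means between the groups at visit 10". The article mentions no fixed or random hospital effect and no stratified test, and it does not explain the omission. Continuous secondary outcomes are also to be analysed by MMRM.

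Under Sample size, the article says "we used a conservative estimate of 0.6 for the standardized treatment effects for between-group differences", that "the minimum required sample size with minimum power set at 0.8 was estimated as 45 subjects per group", and that this was raised to 60 per group to allow for dropout.

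**The concern.** A factor that restricts the randomization normally belongs in the analysis model. Balancing the arms within hospital removes between-hospital variation from the true sampling error of the treatment difference. A model without hospital leaves that variation in the residual, so it reports more uncertainty than the design has.

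Hospital differences are plausible here. The sites range from a neurology and psychiatry center to university and general hospitals, each recruits through its own advertising and referrals, and therapists may be physicians or psychologists. Adjusting for baseline IBS-SI-J need not remove all of this.

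At stake are a slightly wide confidence interval, a test that runs below its nominal level, and a little lost power for the primary comparison. The article lists the model terms explicitly, so the mismatch lies in stated text and is not merely detail left to an unseen analysis plan.

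**Working it through.** **Inputs from the protocol article.** Five centers and two equal groups (Design); stratification by hospital (Randomization); the listed fixed effects and the visit-10 contrast (Statistical analysis); standardized effect 0.6, power 0.8, 45 per group raised to 60 (Sample size).

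**Assumptions, not in the article.** Two-sided alpha of 0.05. A share f of the visit-10 residual variance, after baseline adjustment, lies between hospitals. The total residual SD is 1, the scale on which the effect is 0.6. The treatment effect is the same in all hospitals. There is no dropout.

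**Step 1: reproduce the stated sample size.** The normal approximation gives n = 2(1.960 + 0.842)²/0.6² = 43.6, so 44 per group. The exact noncentral-t calculation gives power 0.795 at 44 and 0.804 at 45, so 45 per group, as stated. That calculation has no center term and is unaffected by this point.

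**Step 2: closed form, allocation balanced within hospital.** With hospital omitted, the reported SE is sqrt(2/n). The true SE is sqrt(2(1 − f)/n). Their ratio is 1/sqrt(1 − f).
- Type I error with hospital omitted: 2[1 − Φ(1.96/sqrt(1 − f))].
- Power with hospital omitted: Φ((0.6 − 1.96 × reported SE)/true SE).
- Power with hospital included: Φ(0.6/true SE − 1.96).

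At n = 60 per group the reported SE is sqrt(2/60) = 0.1826.

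| f (assumed) | true SE | SE ratio | type I error, omitted | power, omitted | power, included |
|---|---|---|---|---|---|
| 0 | 0.1826 | 1.000 | 0.050 | 0.908 | 0.908 |
| 0.02 | 0.1807 | 1.010 | 0.048 | 0.910 | 0.913 |
| 0.05 | 0.1780 | 1.026 | 0.044 | 0.913 | 0.921 |
| 0.10 | 0.1732 | 1.054 | 0.039 | 0.919 | 0.934 |
| 0.20 | 0.1633 | 1.118 | 0.028 | 0.931 | 0.957 |

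At 45 per group and f = 0.10, power is 0.825 omitted and 0.851 included.

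**Step 3: simulation with five hospitals.** The visit-10 contrast was simulated as a baseline-adjusted ANCOVA with 24 participants per hospital and 10,000 runs per setting.

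*Permuted blocks of 4:*
- f = 0.10: mean reported SE 0.181 against a true 0.175 (ratio 1.034); type I error 0.044 omitted, 0.051 included; power 0.922 omitted, 0.934 included.
- f = 0.20: 0.179 against 0.165 (ratio 1.085); type I error 0.035 omitted, 0.049 included; power 0.926 omitted, 0.951 included.
- The mean estimate was 0.600 to 0.604 for a true 0.6, so there is no bias.

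The inflation is smaller than in closed form because only five hospitals are sampled.

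*Unrestricted allocation within hospital:*
- f = 0.20, hospital omitted: reported SE 0.180, type I error 0.049 and power 0.908; including hospital raises power to 0.944.
- f = 0.10: power 0.899 omitted, 0.915 included.

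Here the SE is about right without hospital, and the only cost of omission is power.

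**The case against.** The strongest case on the other side is that the effect is small, conditional and in the safe direction. The article gives no between-hospital variance, so f is wholly assumed. Common TAU guidance, treatment manuals, therapist training and supervision, together with baseline adjustment, may leave little of it. No blocking is stated, and without within-hospital balance the SE is essentially correct. Power at 60 per group is about 0.90 or more before dropout either way, against a target of 0.80. All of this stands and limits the size of the point. It does not remove the mismatch, because balance within hospital is the usual purpose of stratifying.

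Some stronger readings are tempting, and the document does not support them.
- *The analysis discards the stratification.* It does not: the achieved balance remains and the estimate is unbiased.
- *The SE is simply wrong, with a risk of false positives.* It is wrong only under the two conditions above, and then it is too large, so type I error falls.
- *Omission equals losing about a tenth of the sample.* At f = 0.10 the omitted-hospital power of 0.919 matches a model with hospital at 2 × 0.9 × ((1.960 + 1.398)/0.6)² = 56.4 per group, a cost of about 3 to 4 per group, not 6.
- *The common baseline slope across visits also misadjusts visit 10.* Nothing in the article shows this. With equal SDs and baseline correlation ρ, the slope of change on baseline is ρ − 1, which becomes stronger, not weaker, as ρ falls over time.

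**Conclusion.** The mismatch holds: the design stratifies by hospital and the listed primary model leaves hospital out. It is a small to moderate matter of consistency and efficiency, not of validity. The SE excess runs from nothing, if hospitals do not differ or allocation is not balanced within hospital, to about 5% in closed form at an assumed 10% hospital share. Even at a 20% share it is about 9% in simulation and 12% in closed form. The primary test is then mildly conservative and gives up one to three points of power at 60 per group. These figures rest on the assumed f, two-sided alpha of 0.05, a common treatment effect across hospitals and no dropout.

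**What to change.** Add hospital, the randomization stratum, as a fixed effect in the primary MMRM, alongside treatment, visit, treatment-by-visit and baseline IBS-SI-J. Use the same term in the MMRMs for the continuous secondary outcomes. If hospital is left out on purpose, state why.

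The cost is one line of wording and 4 degrees of freedom out of about 120 participants, with no new data and no change to the 45 or 60 per group. With allocation balanced within hospital, the term costs practically nothing even if hospitals do not differ. With unrestricted allocation and no hospital differences it can cost one to two points of power (in simulation, 0.906 to 0.891 with 120 participants spread unevenly over hospitals, and 0.790 to 0.773 with 18 per hospital). Stating whether allocation is blocked within hospital would settle which case applies.

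The change should be fixed before outcomes are compared by arm. In an open-label trial with a self-reported primary outcome, adding a covariate afterwards would look like model selection.
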